### Sample size {14}

Sample size is based on calculations using the outcome measure of proportion of young fathers who apply positive parenting behaviors. Based on the pilot studies on REAL Fathers intervention in Uganda, and to ensure sufficient statistical power of sub-group analyses at the regional level to obtain the largest sample size necessary, we assume only 40% of the young fathers use positive parenting skills at baseline [40]. From pilot studies, the REAL Fathers intervention should improve this proportion by at least 10% (effect size on absolute scale) by the endline [40]. The sample size computation is based on the formula:$$n=\frac{[2*{\left({Z}_{\alpha /4}+{Z}_{1-\beta }\right)}^{2}*\overline{P }(1-\overline{P })]}{{({P}_{1}-{P}_{0})}^{2}}\times Deff$$where:

*n* = minimum sample size of individuals required per arm of study

*Z*_α/4_ = the critical value of the standard normal variate at significance level of α/4 (*α* is assumed to be 0.05 or 95% certainty for improvement in the four primary outcome indicators). By setting the critical *Z* value corresponding to an alpha level of 0.0125 (i.e., α/4), our sample size calculation adjusts for multiple outcome testing while maintaining an overall 5% level of statistical significance for the trial.

*Z*_1-β_ = the critical value of the standard normal distribution at a power of 1-β (assumed to be 0.80 or 80% power)

*P*_0_ = the value of positive parenting indicator at the baseline; assumed 40%

*P*_1_ = the value of positive parenting indicator at the endline; assumed to be 50%—a 10-percentage point increase based on pilot studies$$\overline{P } = \frac{{P}_{1}+{P}_{0}}{2}$$

*Deff* = clustering effect, assumed to be 2.3

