Based on the Uganda Bureau of Statistics 2019 population projections and Uganda Demographic and Health Survey 2016 data, only 4% of the male population (16–25 years) are young fathers who are married or cohabiting [6]. According to the latest Uganda population and housing census, the average village size is about 100 households [49]. Thus, no more than 10 young men (16–25 years) will be fathers whose eldest child is below the age of three years. To be on the conservative side, we assume that, on average, only 8 young fathers are eligible for the study from any given village. Let $$\overline{m }$$ denote this average and suppose *cv* is the coefficient of variation in the number of fathers across the different villages, and ρ is intra-cluster correlation (ICC). Pilot studies on the REAL Fathers intervention approximated ICC of 0.20–0.24 at the village level. Thus:$$Deff=\left(1+\left(\left({cv}^{2}+1\right)\overline{m }-1\right)\rho \right)=\left(1+\left(\left(0.063+1\right)\times 7-1\right)\right)\times 0.20=2.3$$

Based on the above parameters and an attrition rate of 10% between the baseline and endline, a total of 1872 couple dyads is required per study arm (3744 in total). This translates to 156 couples per district: 78 in each study arm from 6 villages; and 312 couples per geographical region. This makes an assumption of treatment effect size of 10% on indicators at project level and 80% statistical power and 95% certainty (alpha = 0.05).

The study is being conducted across regions characterized by diverse subcultures, both between and within locations. To ensure sufficient power to detect potential heterogeneity in treatment effects across key subcultural groups, we adjusted the sample size accordingly. Drawing on pilot data, we anticipate a moderate level of effect heterogeneity across these subcultures. According to Ford and Norrie (2016) [50] and Kent et al. (2018) [51], moderate heterogeneity corresponds to a coefficient of variation (CV) of approximately 20% in treatment effects. To account for this, we increased the originally planned sample size by 20%, resulting in a target of 2200 participants per study arm.

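### The 1872 couples per arm and the 80% power attached to them do not follow from the printed formula and inputs, which give 1,202 per arm (1,411 if the test is two-sided)

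*Protocol article*

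**What the plan says.** All of this stands in the protocol article, Sample size {14}, unless another section is named.

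- The formula returns the "minimum sample size of individuals required per arm of study".
- The critical value is "the critical value of the standard normal variate at significance level of α/4", "corresponding to an alpha level of 0.0125 (i.e., α/4"), because there are four primary outcomes. Sidedness is not stated.
- Power is "assumed to be 0.80 or 80% power".
- P0 is "the value of positive parenting indicator at the baseline; assumed 40"%, and P1 is 50%.
- The design effect is the "clustering effect, assumed to be 2.3".
- The result: "Based on the above parameters and an attrition rate of 10% between the baseline and endline, a total of 1872 couple dyads is required" per arm, 3744 in total. The text attaches "80% statistical power and 95% certainty (alpha = 0.05") to this size and a 10-point effect.

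The section takes 8 eligible fathers per village as its average and 10 as its ceiling, with a village-level ICC of 0.20 to 0.24. Its design-effect equation uses 7 per village and an ICC of 0.20. It then describes 78 couples per arm in each district, drawn from 6 villages. Recruitment {15} describes 24 villages per district.

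**The concern.** The section offers a complete derivation: a formula, every input, an attrition allowance and an answer. A reader can therefore check it, and the answer is well above what the inputs produce. Nothing in the text explains the excess.

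The figure matters because 1872 per arm is the recruitment target in Trial design {8} and Recruitment {15}, and it is presented as what 80% power requires. If the design effect of 2.3 is right, the power statement is too low. If the design effect was larger, the printed one is wrong and the trial has little or no reserve. Readers who judge a null result, or who judge how precise the trial was meant to be, need to know which applies.

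**Working it through.** **Inputs** (all from Sample size {14}): P0 = 0.40, P1 = 0.50, so the mean is 0.45 and the difference 0.10; power 80%, z = 0.8416; design effect 2.3; attrition 10%. The critical value is z = 2.2414 if the printed Z at α/4 is taken literally (0.0125 in one tail), or z = 2.4977 if 0.0125 is a two-sided level.

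**The design effect.** With 7 per village, squared cv 0.063 and ICC 0.20: 1 + (1.063 × 7 − 1) × 0.20 = 2.288, which rounds to the stated 2.3. As printed, the last bracket of the equation closes too early, so that everything is multiplied by 0.20. That would give 7.441 × 0.20 = 1.49. The stated 2.3 is the result of the intended form.

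**The required size**, as 2 × (z + 0.8416)² × 0.45 × 0.55 / 0.10² × 2.3 / 0.9:

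| Reading of Z | Before clustering | × 2.3 | / 0.9 | 1872 relative to this |
|---|---|---|---|---|
| Literal, 2.2414 | 470.5 | 1,082 | 1,202 | 56% larger |
| Two-sided 0.0125, 2.4977 | 552.0 | 1,270 | 1,411 | 33% larger |

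The stated 1872 is not reproduced.

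**Other mixes of stated inputs:**

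- 8 per village (the text's average), ICC 0.20: design effect 2.50, giving 1,307, or 1,534 two-sided.
- 8 per village, ICC 0.24, two-sided: design effect 2.80, giving 1,718. This is the least favourable mix that keeps the stated average.
- The 20% heterogeneity increase at design effect 2.3: 1,443, or 1,693 two-sided. The text applies that increase to the originally planned size to reach 2200, so it is not part of 1872 in any case.

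**Power at 1872 on the printed inputs.** The effective number per arm is 1872 × 0.9 / 2.3 = 732.5. The standardised difference is 0.10 × √(732.5 / 0.495) = 3.847.

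- Literal: 3.847 − 2.241 = 1.605, power 94.6%.
- Two-sided: 3.847 − 2.498 = 1.349, power 91.1%.
- Difference detectable with 80% power: (z + 0.8416) × √(0.495 / 732.5) = 8.0 points, or 8.7 two-sided.

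**Design effect needed for 1872 to be the answer at 80% power.** 1872 × 0.9 / 470.5 = 3.58, or 1872 × 0.9 / 552.0 = 3.05 two-sided.

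**Couples per village in the document:**

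| Source | Per village |
|---|---|
| Sample size text, average | 8 |
| Design-effect equation | 7 |
| Sample size layout, 78 / 6 | 13 |
| Recruitment {15}, 24 villages split equally: 78 / 12 | 6.5 |

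At 13 per village and ICC 0.20 the design effect is 1 + (1.063 × 13 − 1) × 0.20 = 3.56. The required size is then 470.5 × 3.56 / 0.9 = 1,863. Over 24 sub-counties per arm that is 77.6, which rounds up to 78, and 78 × 24 = 1872. Power at 1872 is about 80%, or 72% two-sided. At ICC 0.24 the design effect is 4.08 and power is 74%, or 65% two-sided.

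**The case against.** **The error is on the safe side.** On the printed inputs enrolment exceeds the requirement, and no estimand, model or decision rule changes. This stands and lowers the weight of the point. The comfort does depend on the design effect of 2.3, which the document's own layout of 13 per village does not support.

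**An unprinted allowance may explain the gap.** The section mentions power for regional subgroups. That phrase accompanies the choice of the 40% baseline value, and no regional factor appears in the formula. An undescribed allowance is possible, but it would not make 1872 follow from the stated parameters.

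**Three stronger readings go too far:**

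- A reader might infer that a design effect of 3.56 was the one used. It fits, but so does another set: 10 per village, ICC 0.21 and a two-sided test give a design effect of 3.02 and a size of 1,854, again 78 per sub-county after rounding up. Also, 13 per village exceeds the plan's own ceiling of 10.
- A reader might infer that the trial has 95% power. That holds only if clustering is at village level with a design effect of 2.3. Randomisation is by sub-county, and the document gives no sub-county ICC.
- A reader might see a contradiction between the alpha of 0.05 beside the final size and the 0.0125 in the formula. The section defines α as 0.05 for the trial overall and divides it by four for each outcome. The two statements agree.

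**Conclusion.** The mismatch is confirmed. The printed formula and inputs require 1,202 couples per arm, or 1,411 two-sided, and no mix of inputs that keeps the stated average of 8 per village (or the equation's 7) reaches 1872. The conclusion does not depend on sidedness. The stated size and the stated 80% power therefore do not belong together on the printed assumptions.

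The document does not show which input differs. Depending on the cluster size, the same 1872 corresponds to about 95% power or about 80%, and to less than 80% if the test is two-sided or the ICC is at the upper end with 13 per village. All these figures assume village-level clustering only and a comparison of two proportions at one time point, as in the printed formula. The finding does not show that 1872 is too many or too few. It is a reporting fault in a figure that others rely on, and correcting the text is enough.

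**What to change.** Leave enrolment unchanged and make the calculation reproducible:

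1. Reconcile the number of villages per arm and the couples per village between the Sample size and Recruitment sections.
2. State the sidedness, cluster size, ICC and design effect actually used, and correct the brackets in the design-effect equation.
3. From that one set, restate the required size and the power at 1872 (or the difference detectable with 80% power).

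Neither 3.56 nor 95% should be printed unless the sponsor confirms the inputs behind it. The overall alpha of 0.05 can stay. A note that each primary outcome is tested at 0.0125 would help.

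The cost is a change of wording and one recalculation by the trial statistician, with no effect on participants.

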### Trial design {8}

The impact of the REAL Fathers intervention will be assessed using a cluster-randomized controlled trial (cRCT) wait-list control rollout design [44]. This cRCT employs a superiority framework to test the null hypothesis that there will be similar differences in the primary and secondary outcomes from baseline to endline in both the REAL Fathers intervention group and the waitlisted control group receiving standard care [45]. The survey questionnaire will use validated questions, as piloted in a previous evaluation of the intervention [40], and will be extended to include items from Caregiver Reported Early Development Instruments (CREDI) [46] and socio-demographic items adapted to the local context. The phased rollout of the study will involve three cohorts, each with 1872 father-spouse dyads in the control group and 1,872 father-spouse dyads in the intervention group, for a total of 3744 father-spouse dyads across the three cohorts and study arms. Baseline data collection will occur roughly one month before the start of a cohort, with endline data collection occurring roughly 8 months later (i.e., one month after the 7-month mentoring period of the REAL Fathers intervention ends). Follow-up data collection will occur 8 months after endline data collection. This rollout design is optimal for resource constraint and ethical considerations. The trial is designed to match the speed of implementation, with a random sample of study participants in the intervention group selected from the overall implementation cohorts. Due to personnel and resource constraints in reaching the large number of program beneficiaries, staggered implementation of the intervention—and therefore also the cRCT trial which uses a sub-sample of program beneficiaries—is necessary. Further, from an ethical standpoint, in order to offer those in the control conditions of the study an opportunity to participate in REAL Fathers, several implementation cohorts are necessary, making this wait-list control rollout design the most appropriate for the study context.

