### Recruitment {15}

A combination of listing and stratified simple random sampling approaches will be applied while selecting study participants. The participants will be recruited within the 24 districts (four districts in each region). In each district, a three-stage sampling design will be applied. In the first stage, two sub-counties will be selected at random considering the urban/rural divide (see Table 7). From the selected sub-counties, up to four parishes will be selected at random. From each selected parish, up to 12 villages will be selected at random and a census/listing of all eligible young fathers as per the inclusion criteria (Table 2, above) will be listed with the help of individuals familiar with the villages (i.e., members of village health teams (VHTs) and village leaders (local council chairpersons or LC1 executives) to generate a sampling frame. A total of 24 villages will be sampled from 4 randomly selected parishes in two randomly selected sub-counties in each district.

**Table 7 Tab7:** REAL Fathers external evaluation selected sample

	**District**	**Sub-county**	**Randomization**
1	Amuria	Akeriau	Intervention
2	Amuria	Morungatuny	Control
3	Bugiri	Bulidha	Intervention
4	Bugiri	Iwemba	Control
5	Buikwe	Nkokonjeru Tc	Intervention
6	Buikwe	Buikwe Tc	Control
7	Dokolo	Okwalongwen	Intervention
8	Dokolo	Agwata	Control
9	Hoima	Kyabigambire	Intervention
10	Hoima	Kigorobya	Control
11	Ibanda	Keihangara	Intervention
12	Ibanda	Ishongororo	Control
13	Iganga	Nawanyingi	Intervention
14	Iganga	Nakalama	Control
15	Isingiro	Kabuyanda	Intervention
16	Isingiro	Kashumba	Control
17	Kamuli	Bulopa	Intervention
18	Kamuli	Kagumba	Control
19	Katakwi	Katakwi	Intervention
20	Katakwi	Toroma	Control
21	Kayunga	Kangulumira	Intervention
22	Kayunga	Kayunga	Control
23	Kikuube	Bugambe	Intervention
24	Kikuube	Kiziranfumbi	Control
25	Kiryandongo	Bweyale Tc	Intervention
26	Kiryandongo	Kiryandongo Tc	Control
27	Kole	Ayer	Intervention
28	Kole	Bala	Control
29	Lira	Aromo	Intervention
30	Lira	Ogur	Control
31	Luwero	Bamunanika	Intervention
32	Luwero	Katikamu	Control
33	Masindi	Miirya	Intervention
34	Masindi	Pakanyi	Control
35	Mayuge	Imanyiro	Intervention
36	Mayuge	Mpungwe	Control
37	Mbarara	Kagongi	Intervention
38	Mbarara	Kashare	Control
39	Nakasongola	Nabisweera	Intervention
40	Nakasongola	Wabinyonyi	Control
41	Oyam	Ngai	Intervention
42	Oyam	Otwal	Control
43	Rubirizi	Katerera	Intervention
44	Rubirizi	Kirugu	Control
45	Serere	Kateta	Intervention
46	Serere	Kyere	Control

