47	Soroti	Tubur	Intervention
48	Soroti	Asuret	Control

A total of 3744 young fathers and their spouses (i.e., couple dyads) will be recruited (1872 per study arm) for this study, or 156 young fathers and their spouses per district. Study participants will be recruited solely through household visits. All young fathers and their spouses willing to follow the study protocol will go through an informed consent process. In a first step, fathers who meet the study’s eligibility criteria will be contacted and briefly informed about the study and invited for an interview. If consent is obtained, the young father’s female partner (either his spouse or cohabitating girlfriend) will be informed about the study and invited for an interview either on the same day or at a later scheduled date. If both the young father and the female partner agree to take part in the study, written informed consent will be obtained from both.

If the couple is not available on the initial day of contact, up to two additional attempts (for a maximum of three visits) will be made to contact the couple on varying days of the week. If the couple declines to participate or cannot be located after the third visit, a new young father will be randomly selected from the village listing. We will use randomization without replacement to reach the required sample.

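### The 1,872 dyads per arm do not follow from the stated inputs, and the 2,200 target and the village, region and cohort counts are not reconciled with it

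*Protocol article*

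**What the plan says.** All references are to the protocol article.

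- **Sample size, inputs.** The formula gives individuals per arm for 40% versus 50%, with 80% power and a design effect of 2.3. Its critical value is "the critical value of the standard normal variate at significance level of α/4", and the text confirms a z "value corresponding to an alpha level of 0.0125 (i.e., α/4"). Whether the test is one- or two-sided is not said.
- **Sample size, result.** With 10% attrition, "a total of 1872 couple dyads is required per study arm (3744 in total"). This is broken down as 156 couples per district: "78 in each study arm from 6 villages; and 312 couples per geographical region". The paragraph closes by citing 80% power and alpha 0.05.
- **Sample size, last paragraph.** A 20% increase for effect heterogeneity follows, "resulting in a target of 2200 participants per study arm".
- **Recruitment.** The 3,744 couples "will be recruited (1872 per study arm) for this study", at 156 per district. On villages: "A total of 24 villages will be sampled from 4 randomly selected parishes in two randomly selected sub-counties in each district".
- **Trial design.** There are "three cohorts, each with 1872 father-spouse dyads in the control group and 1,872 father-spouse dyads in the intervention group". The same sentence then gives 3,744 as the total over cohorts and arms.

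**The concern.** A sample size paragraph should let a reader rebuild the number from its inputs. Here the inputs are all printed and the number is said to follow from them, but it does not. A second target then appears and is not carried into the sections that govern recruitment. The counts that turn the target into fieldwork (villages, couples per village, couples per region, cohorts) disagree with one another.

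Two things are at stake. Enrolment is stated to be active, so the number at which recruitment ends is a live question. The number of couples per village also sets the design effect, so the power claim cannot be judged until the village count is settled.

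**Working it through.** **1. The plan's formula with the plan's inputs.** P0 = 0.40, P1 = 0.50, mean 0.45, so mean × (1 − mean) = 0.2475 and the squared difference is 0.01. The power term is z = 0.842.

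n before clustering = 2 × (z + 0.842)² × 0.2475 / 0.01. Multiply by 2.3 for clustering and divide by 0.9 for attrition.

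| Reading of alpha | z | n before clustering | × 2.3 | ÷ 0.9 |
|---|---|---|---|---|
| alpha/4 read literally | 2.241 | 470.5 | 1,082 | **1,202** |
| two-sided 0.0125 | 2.498 | 552.0 | 1,270 | **1,411** |
| two-sided 0.05 (the closing sentence) | 1.960 | 388.5 | 894 | 993 |

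The stated 1,872 is not reproduced. It is 56% above 1,202 and 33% above 1,411. To reach it, the design effect would have to be 1,872 × 0.9 / 470.5 = 3.58, or 1,872 × 0.9 / 552.0 = 3.05.

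**2. Power at 1,872 on the stated inputs.** Power = Φ(√[n × 0.9 / Deff × 0.01 / (2 × 0.2475)] − z). With Deff 2.3 the square root is 3.847. Power is therefore Φ(3.847 − 2.241) = 95%, or Φ(3.847 − 2.498) = 91%.

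**3. The design effect line.** The text assumes 8 eligible fathers per village, but the equation uses 7. As bracketed in print it is (1 + (1.063 × 7 − 1)) × 0.20 = 1.49. Bracketed correctly it is 1 + (1.063 × 7 − 1) × 0.20 = 2.29, which is the 2.3 quoted. With 8 it would be 2.50.

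**4. The second target.** 1.2 × 1,872 = 2,246. A target of 2,200 is 17.5% above 1,872. If its unit is couples, the difference from the recruitment total is 2 × 2,200 − 3,744 = 656 couples.

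**5. The counts.**
- District: 78 × 24 = 1,872 per arm, which agrees.
- Region: 156 × 4 = 624 couples. The printed 312 is 78 × 4, the figure for one arm.
- Cohorts: 2 × 1,872 = 3,744 is the sum over all cohorts, not the size of each.
- Villages: 78 / 6 = 13 couples per village in Sample size. Recruitment has 24 villages over two sub-counties, about 12 each if split evenly, so 78 / 12 = 6.5 couples per village.

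**6. What the village count does.** 1,872 per arm, two-sided 0.0125, 10% attrition, the plan's cv² of 0.063 and its ICC range:

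| Villages per sub-county | Couples per village | Deff (ICC 0.20 / 0.24) | Power (ICC 0.20 / 0.24) |
|---|---|---|---|
| 12 | 6.5 | 2.18 / 2.42 | 93% / 90% |
| 6 | 13 | 3.56 / 4.08 | 72% / 65% |

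**The case against.** The strongest reply is that 1,872 exceeds what the formula asks for, so the error is conservative and no estimate or test is affected. That stands for the stated design effect of 2.3. It does not stand for the 6-village allocation printed in the same section.

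A second reply is that the number can be rebuilt. With 13 couples per village and ICC 0.20 the design effect is 3.56, and z = 2.241 then gives 1,863 per arm. Dividing by 24 gives 77.6, which rounds up to 78, and 78 × 24 = 1,872. With z = 2.498 the same design needs 2,186, close to 2,200. Each target therefore has about 80% power under one reading, and it would be wrong to say that 80% fits neither. But that reading contradicts the stated 2.3 and the 8 eligible fathers per village, so it does not rescue the derivation as written.

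A reader might also infer more than the documents support:
- **That the trial is underpowered or cannot recruit** (6 × 8 = 48 eligible against 78 needed). This holds only if 6 villages per sub-county is the real plan. Recruitment's 24 per district points to 12. Enrolment in three waves also means that the eligible pool is not fixed.
- **That 3 × 3,744 = 11,232 couples are planned.** The Trial design sentence itself totals 3,744, so this is a wording slip.
- **That the 2,200 paragraph should simply be deleted, or that each cohort has 624 per arm.** The paragraph has a stated purpose. The documents do not show which target is current, and they do not say that the cohorts are equal.

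**Conclusion.** The point holds as an untraceable derivation with an unreconciled second target. The stated inputs give 1,202 or 1,411 per arm, not 1,872, and at 1,872 they imply about 91–95% power. Most of the document (Abstract, Recruitment, and the total in Trial design) supports 3,744 couples, and only one paragraph says 2,200. The 312 per region and the per-cohort wording are labelling errors that need correcting but are not competing targets.

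The village count is the part with a real consequence, because it moves power from about 90–93% to 65–72% at two-sided 0.0125. These power figures take the plan's village-level design effect, ICC range, cv and attrition as given, and assume villages split evenly between the two sub-counties of a district. They do not show that the trial is underpowered. They show that the document does not settle whether it is.

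**What to change.** 1. State one recruitment target in every section, in couples. 1,872 per arm fits the Abstract and Recruitment and needs no extra participants. If 2,200 is current, revise those sections and the Trial design total, correct the 20% arithmetic, and budget for 656 more couples (if the unit is couples). The choice is the sponsor's.
2. State whether the test is one- or two-sided, give the z value used, and replace the closing alpha of 0.05 with 0.0125 per outcome.
3. Give the design effect with correct brackets and the number of couples per village actually planned, over the ICC range 0.20–0.24.
4. Report what the formula then yields and the power at the chosen target.
5. Reconcile the villages per sub-county between Sample size and Recruitment. Label 312 as per arm (624 couples per region). Reword Trial design so that 1,872 per arm is the sum over the three cohorts.

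If 1,872 and 12 villages per sub-county are confirmed, the cost is protocol wording only.

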**Methods:**

To assess the REAL Fathers intervention, we use a cluster-randomized controlled trial design within 48 sub-counties randomly sampled from 24 districts in six regions of Uganda. Sub-counties were randomly allocated to treatment or control arms at baseline. Study participants are fathers ages 16–25 years and their cohabitating wives whose eldest child is below the age of 3 years (*n* = 3744 couple dyads). Primary outcomes are the following: (1) reduced intimate partner violence; (2) reduced violent discipline of children; (3) increased father-child engagement and play; (4) improved early childhood development. Secondary outcomes include the following: (1) father’s knowledge of and (2) attitudes towards positive parenting and discipline; (3) father’s use of positive parenting and discipline; (4) father’s use of emotional engagement with child; (5) couple communication and conflict resolution; (6) gender equitable household and caregiving decision-making and behaviors; (7) father engagement in child health-promoting activities; (8) improved knowledge of family planning methods; (9) reduced unmet need for family planning; (10) reduced problem alcohol use; and (11) supportive community norms for father-child engagement and play. Longitudinal survey data will be collected by trained enumerators using KoboCollect in six local languages at three time points: one month before the intervention (baseline); one month after the intervention (endline); and nine months after the intervention (follow-up). Intervention effects on primary and secondary outcomes will be assessed using difference-in-differences (DiD) mixed-effects models that account for the clustered design.

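### The protocol sets the target at 2200 per arm in one sentence and 1872 per arm everywhere else; recruiting to the stated quotas stops 14.9% short of the larger figure

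*Protocol article*

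**What the plan says.** The Sample size section gives two targets in succession. From the stated parameters and 10% attrition it first concludes that "a total of 1872 couple dyads is required per study arm (3744 in total"), and converts this to field quotas: "This translates to 156 couples per district: 78 in each study arm from 6 villages; and 312 couples per geographical region". Its closing paragraph, about differing treatment effects across subcultures, then reports a completed change: "we increased the originally planned sample size by 20%, resulting in a target of 2200 participants per study arm".

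The other sections that give a size use the smaller number:

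- Abstract, Methods: "3744 couple dyads".
- Trial design: "for a total of 3744 father-spouse dyads across the three cohorts and study arms". The same sentence can be read as 1872 per arm in each of three cohorts, but its own total shows that 1872 is the overall figure per arm.
- Recruitment: "A total of 3744 young fathers and their spouses (i.e., couple dyads) will be recruited (1872 per study arm) for this study", with a quota of "156 young fathers and their spouses per district".
- Data management: a quality-control sample of about 1%, given as 37 respondents.

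No section reconciles the two targets, labels either as superseded, or gives district or village quotas for 2200.

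**The concern.** The enrolment target is a core item of any protocol, and here two current statements of it differ by 656 couples. The larger one is written as a decision already taken, for a stated purpose: power to detect heterogeneity of effect. The smaller one is what the field teams are told to deliver. If they follow the Recruitment section, the extra couples are never enrolled, while the published protocol says that they were planned for.

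This bears on interpretation because stratified analyses by region are planned, and the Discussion says the trial is powered for them. A reader of the regional results would believe that the sample had been enlarged for that purpose. Whether recruitment met its target would also depend on which sentence is consulted.

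**Working it through.** **Inputs.** From Sample size: 1872 dyads per arm, 2200 per arm after a 20% increase, 78 per arm per district, 312 per region. From Recruitment: 3744 in total, 156 per district. From Study setting and Table 7: 24 districts in 6 regions, with one intervention and one control sub-county per district. From Data management: quality-control sample of about 1% = 37.

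**Step 1: is 2200 an increase on 1872?** 1872 x 1.20 = 2246.4. The stated 2200 is 46 lower, a 2.1% difference. 2200 / 1872 = 1.175, a 17.5% increase. So 2200 is a loosely rounded 20% increase, and 1872 is the base it was applied to.

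**Step 2: which target do the quotas deliver?**

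| Quota | Calculation | Result |
|---|---|---|
| Per arm per district | 78 x 24 | 1872 per arm |
| Per district | 156 x 24 | 3744 in total |
| Per region | 312 x 6 | 1872 (312 = 4 x 78, so a per-arm figure) |
| Quality-control sample | 1% of 3744 | 37 |

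For 2200 per arm (4400 in total) the corresponding figures would be 2200 / 24 = 91.7 per sub-county, 4400 / 24 = 183.3 per district, 2200 / 6 = 366.7 per arm per region, and a 1% sample of 44. None of these appears.

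**Step 3: size of the gap.** 2200 - 1872 = 328 per arm, or 656 in total. 1 - 1872 / 2200 = 14.9%. Against an exact 20% increase the gap is 2246 - 1872 = 374 per arm, or 16.7%.

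**Step 4: could the change of unit explain it?** The 2200 is in participants and the 1872 in couple dyads. But 1872 dyads are 3744 individuals per arm, so 2200 individuals would be a reduction. The unit does not reconcile the figures.

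**Step 5: effect on the main comparison.** Take 40% versus 50%, Deff 2.3, 10% attrition and alpha 0.0125. The plan does not state sidedness; two-sided is assumed here.

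- At 1872: effective n = 1872 x 0.9 / 2.3 = 732.5 per arm, power about 91%.
- At 2200: effective n = 2200 x 0.9 / 2.3 = 860.9 per arm, power about 95%.

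Both exceed the planned 80%.

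**The case against.** The strongest reply is that 1872 may already contain the 20%, which would make 2200 the stray figure. The base number does not follow from the plan's formula, n = 2(z + z)² P̄(1 - P̄) / (P₁ - P₀)² x Deff, divided by 0.9 for attrition. With Deff 2.3 it gives about 1202 per arm with z at 0.0125 one-sided, or 1411 two-sided.

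Other inputs named in the same section come closer once 20% is added (alpha 0.0125 two-sided):

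- A mean of 8 fathers per village with ICC 0.20 gives Deff 2.50 and 1534 per arm. Then 1534 x 1.2 = 1841, or 12.8 per village over 6 x 24 = 144 villages. Rounding up to 13 gives 13 x 144 = 1872.
- A mean of 7 with ICC 0.24 gives Deff 2.55 and 1561 per arm. Then 1561 x 1.2 is about 1874.

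The arithmetic is right, but the reading does not clear the text. It needs a Deff other than the stated 2.3; at 2.3 even the inflated sizes are only about 1443 and 1693. It also reverses the order of the section, which obtains 1872 from the parameters and attrition and only then describes the increase. And if it were true, the sentence giving 2200 would still be wrong. What stands is that the sponsor must say whether the 20% lies inside 1872 or on top of it.

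Other parts of the reply are fair. The Recruitment section on its own is clear, and a single sentence is the outlier. The gap between 17.5% and 20% and the switch from dyads to participants are minor. The main comparison keeps its power. None of this removes the contradiction.

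**Conclusion.** The concern holds. The plan gives two incompatible enrolment targets, and every quota serves the smaller one. Recruiting as instructed yields 1872 dyads per arm, which is 328 per arm (656 in total, 14.9%) below the target the plan says it set.

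This takes the Sample size section in its written order, with 1872 as the base for the increase. If 1872 already includes the allowance, nothing is short, but the statement of 2200 is then false and must go. Either way the text needs correcting. The consequence is confined to the heterogeneity allowance and the accuracy of the stated sample size; no loss of power for the main comparison is shown. That 1872 cannot be reproduced from the plan's own formula is a separate matter on which this conclusion does not depend.

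**What to change.** State one target, in couple dyads, and use it throughout.

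- **If 1872 per arm is confirmed:** keep all quotas and remove the claim that the size was raised to 2200. If the 20% is in fact already inside 1872, say so and show the derivation. Recheck the Discussion's statement about power for regional analyses, since it could no longer lean on the enlargement. The cost is wording, with no extra participants.
- **If 2200 per arm is the approved number:** change the Abstract, Trial design, Sample size, Recruitment and Data management sections to 4400 in total, with about 92 dyads per sub-county, about 183 per district and a 1% quality-control sample of 44. Revisit the village numbers: 78 from 6 villages is 13 each, whereas 92 would be about 15. Correct the percentage as well, since 2200 is 17.5% above 1872 and an exact 20% is 2246. The cost is 656 additional couples.

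The protocol reports enrolment as active at submission, so the choice should be made and dated before recruitment closes. The registered enrolment figure was not available for this review and should be checked against whichever number is kept.
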